### **10.7. Serious Adverse Event Reporting**

Any serious adverse event must be reported to the sponsor and, where required, the relevant ethics committee within 24 hours of the onset of the event. Full details of the event, treatment, and an assessment of the relationship to study procedures must be provided in the report.

All serious adverse events will be followed until they are resolved or for 30 days after the subject's participation in the clinical study ends.

The CI should institute appropriate therapeutic and follow-up measures in accordance with good medical practice but should notify the monitor of such actions and record them in the subject's Case Report Form.

### **10.8. Device Deficiencies**

Device deficiencies are defined as 'Any inadequacy of the study device with respect to its identity, quality, durability, reliability, safety or performance'. Device deficiencies include malfunctions, user errors and inadequate labelling. All device deficiencies will be recorded in the CRF. Any deficiency of the device that is considered to constitute a hazard to the safety of users must be reported to the Sponsor within 24 hours of identification.

## 11. Data Collection, Processing and Statistical Analysis

### 11.1. Completion of Data Collection Forms

The Chief Investigator (CI) must maintain required records on all study subjects. Data for this study will be recorded in the subject's medical records, study-specific worksheets and on Case Report Forms (CRFs) provided by the sponsor in accordance with the parameters set forth in ICH Topic E6 for GCP (1.5.96) Guidelines - Responsibilities of Sponsor, Monitor and Investigator, and with 21 CFR Part 812. All data on the CRFs should be recorded from appropriate source documentation. No personal identifiable data will be entered on CRFs. Subjects will be identified only by their unique identification code number. All data recorded on all documents will be regarded as confidential.

The CI must record the subject's participation in this clinical study in the subject's medical notes. In addition, the CI must keep a separate list of all subjects entered into the clinical study showing each subject's name, date of birth and assigned subject number (for identification purposes). A Subject Identification Log will also be provided in the Investigator Site File to record the subject's initials and assigned subject number.

### 11.2. Data Correction

Corrections to data entered on original CRFs must be made in the following manner:

- The correct data should be entered clearly replacing the incorrect entry but maintaining an appropriate audit trail.
- Completed CRFs should be ready for review by the monitor prior to study visit. The Sponsor will review the CRFs, evaluate them for completeness and accuracy, and ensure all corrections are made to either the CRF or other designated clarification form.

### 11.3. Review and Return of Completed Documentation

Upon study completion, or at any other time specified by the sponsor, a monitor will verify the source documentation records and review the data, conducting source document verification. Copies of all CRF pages will remain at the study site with any related data clarification forms (DCF).

### 11.4. Data Protection

The study sponsor, GSTT and KCL, will manage the clinical data in clinical study data management systems that comply with all applicable EU and national standards including International Conference on Harmonization (ICH) Good Clinical Practice Section 5.5 (Trial Management, Data Handling, and Record Keeping) and the UK Data Protection Act (2018).

All data, including imaging data files, will be anonymised before being entered into the study database or being transmitted to the sponsor. All data will be kept for at

least 5 years and backed up in accordance with GCP, national and EU legislation. Data protection and security will be ensured by the local data controller nominated for this task.

Access to the data will be limited to only the primary research team, with access via a key which will be safely kept in a locked draw in the oncology research offices at King's College London, [name]

### 11.5. Record Retention

The investigator will maintain records for this study, which includes subject's CRFs, medical records, laboratory reports, signed informed consent forms, safety reports, plus all other pertinent data. The investigator will retain study medication disposition records, copies of CRFs (or electronic files), and source documents for the maximum period required by the country in which the study will be conducted, or the period specified by the sponsor, whichever is longer.

European Commission Directive 2005/28/EC requires that investigators and sponsors shall retain the essential documents for at least 5 years after completion of a clinical trial.

If the investigator relocates, retires, or withdraws for any reason from the study, trial records may be transferred to an acceptable designee, such as another investigator within the institution. Prior notice of such transfer will be provided in writing to the sponsor. The investigator must obtain written permission from the sponsor prior to disposing of any records.

### 11.6. Data Analysis

#### 11.6.1. Analysed Population

All participants enrolled into the study will be assigned to the following analysis sets:

- The intention to treat (ITT) analysis set. This will comprise all patients assigned to treatment.
- The Per Protocol analysis set. This set will comprise all participants who complete the study according to the protocol and who were compliant with assessment procedures (i.e., completed follow-up visits in accordance with local practice). It includes only those participants whose WLE specimens, and cavity shavings (if any) specimens were imaged within the time-window of approximately 145 minutes post-injection.

Further sensitivity analysis and summaries will be conducted based on sub-sets of the per protocol analysis set: e.g., subsets based on breast cancer diagnosis prior to surgery (invasive/DCIS), age etc.

A summary of the rate of decision to re-operate in the “Delayed LightPath® image set” (any participant for whom LightPath® Image of WLE and any cavity shaving specimens is outside the optimal time-window) will be presented as these participants will be excluded from the per protocol analysis set.

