|                                           | 
surgeon will take a cavity shave of the corresponding margin, provided more tissue can be taken.
 
All LightPath® images will be acquired within approximately 145 minutes post-injection.
 
The WLE specimen and cavity shavings (where performed) will undergo standard of care histopathological analysis.
 
Participants will return for a study completion visit, coinciding with their standard of care surgical follow-up for the MDT decision whether to re-operate (1-2 weeks after completion of the initially planned surgery).
                                                                                                                                                                                                                                                                                                                                                                        |
| Data Analysis for Outcome Measures | 
All patients who pass screening will be included in the intention to treat (ITT) population.
 
The per protocol (PP) population is defined as all patients who completed BCS and study procedures as per protocol description.
 
The primary endpoint will be analysed based on the PP population.
 
The secondary endpoints will be analysed using the PP population and the ITT population.
 
The primary analysis of the study, including analysis of all available study outcomes (primary, secondary and exploratory where data is available), will be conducted after all patients have completed the follow-up visit.
 
Subgroup analysis will be conducted to assess the impact of important subgroups (e.g., breast cancer subtypes, invasive/in situ) on the performance of intraoperative LightPath® CLI + FAR imaging.
 
All outcome measures will be summarised descriptively.
 |

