#### **8.6. Day of surgery**

##### **8.6.1. Radiopharmaceutical administration**

Prior to her surgery, the participant will be prepared for surgery in accordance with the local hospital standard of care. The following information/procedures will be completed on the day of surgery or the day before surgery by a designated team trained in administering radiopharmaceuticals:

- Administration of  $^{99m}\text{Tc}$  tracer prior to the administration  $^{18}\text{F}$ -FDG
- Administration of  $^{18}\text{F}$ -FDG.

Administration of  $^{18}\text{F}$ -FDG will be scheduled accordingly, to ensure the LightPath® images will be taken approximately 145 minutes post-injection of  $^{18}\text{F}$ -FDG.

Work-up and preparation for surgery will be performed as per standard of care.

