### 8.6.4. LightPath® assessment

The WLE specimen will be examined by CLI + FAR LightPath® imaging at the time of the surgical procedure. All LightPath® images will be performed within approximately 145 minutes post-injection of  $^{18}\text{F}$ -FDG. If imaging is delayed for any reason, the reason must be recorded on the CRF. Imaging must be performed without unnecessary delay and following the acquisition times set out in the IFU, in order to avoid any degradation in specimen quality prior to transfer to the tissue bank / pathology department for routine analyses.

The operating surgeon will interpret the recorded CLI + FAR LightPath® Images. It will be at the surgeon's discretion to choose how to act on the CLI + FAR LightPath® images.

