## 11.7. Data Analysis for Outcome Measures

Most data analysis will be descriptive only due to the non-comparative nature of this study. Continuous variables will be summarised descriptively by number of subjects, mean, standard deviation, minimum, and maximum. Categorical data will be summarised descriptively by frequencies along with associated percentages.

The primary outcome measure will be analysed on the per protocol analysis set. All other outcomes will be analysed based on the ITT set and on the per protocol analysis set (unless stated otherwise). The diagnostic performance of the LightPath® Imaging will be evaluated based on the primary endpoint analysis. Any other p-values presented from analysis of secondary endpoints will be used to aid interpretation and will not be adjusted for potential correlation between endpoints or multiple-testing.

Baseline participant characteristics will be summarized descriptively; continuous variables will be summarised descriptively by number of participants, mean, standard deviation, minimum, and maximum; categorical data will be summarised descriptively by frequencies along with associated percentages.

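### Entry to the primary analysis set depends on when cavity shavings were imaged, so exclusion is likely to depend on the LightPath result and can bias sensitivity down and specificity up

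*Protocol*

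**What the plan says.** Section 6.1 defines the primary outcome on the WLE specimen only. Cavity shavings are a separate secondary outcome in section 6.2. Section 11.7 fixes the population: "The primary outcome measure will be analysed on the per protocol analysis set".

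Section 11.6.1 defines that population. Of the per-protocol set it says: "It includes only those participants whose WLE specimens, and cavity shavings (if any) specimens were imaged within the time-window of approximately 145 minutes post-injection". Of participants with a delayed image of the WLE or of any shaving it says that "these participants will be excluded from the per protocol analysis set". The whole participant leaves the set, not just the late specimen.

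The Synopsis (Purpose and Study Procedures) has a positive LightPath image lead to a cavity shaving. The shaving is then imaged itself and may lead to a further one. The Schedule of Events (2.4) also allows a shaving on the basis of specimen x-ray. Sections 8.6.2 and 8.6.4 leave the response to the image to the surgeon.

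Three side issues concern the same sets:
- The per-protocol set also requires participants to be "compliant with assessment procedures (i.e., completed follow-up visits in accordance with local practice").
- The imaging time is a target in section 8.6.1 ("images will be taken approximately 145 minutes post-injection of" FDG) and reads as a limit in section 8.6.4 ("images will be performed within approximately 145 minutes post-injection of" FDG).
- ITT is defined in the Synopsis as "All patients who pass screening will be included in the intention to treat (ITT) population" and in section 11.6.1 as "This will comprise all patients assigned to treatment".

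**The concern.** A WLE image obtained in time and matched to a histopathology result is all that the primary comparison needs. Under section 11.6.1 that pair is discarded if a different, later specimen was imaged late.

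The extra hurdle does not fall evenly. A LightPath-negative patient usually has one specimen to image in time. A LightPath-positive patient may have two or more in sequence, because the shaving is cut after the WLE has been read and then goes through CLI and FAR (section 8.6.6). FDG is scheduled so that imaging falls at about 145 minutes, and no separate window is given for shavings. Membership of the primary set is therefore likely to depend on the result of the test under study.

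At stake are sensitivity and specificity, both primary measures in section 11.7.1, and the true positives, who are few: about 11 among 60 patients on the planning assumptions.

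**Working it through.** **Inputs from the protocol.** 60 enrolled and 54 analysed (11.6.2); about 10% dropped out or not evaluable (11.8); positive margins 20%, sensitivity (Se) 95%, specificity (Sp) 90% (11.6.2). The plan's own figure reproduces: 60 × 0.90 = 54, an allowance of six losses.

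**Assumed inputs.** e+ and e−, the proportions of LightPath-positive and LightPath-negative patients excluded. The protocol gives neither.

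**Expected table for 60 patients, no exclusions.**
- Histology-positive: 60 × 0.20 = 12, of whom 11.4 are true positives and 0.6 false negatives.
- Histology-negative: 48, of whom 43.2 are true negatives and 4.8 false positives.
- LightPath-positive: 11.4 + 4.8 = 16.2. LightPath-negative: 43.8.

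**Formulas when exclusion depends on the LightPath result.**
- Se′ = Se(1−e+) / [Se(1−e+) + (1−Se)(1−e−)]
- Sp′ = Sp(1−e−) / [Sp(1−e−) + (1−Sp)(1−e+)]

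If e+ = e−, both are unbiased: at 10% each, Se′ = 95.0%, Sp′ = 90.0% and N = 54, with 10.8 histology-positive patients. If e+ > e−, Se′ < Se and Sp′ > Sp.

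**Case 1: six losses, with 5% of negatives lost.** The negatives account for 43.8 × 0.05 = 2.19 losses, which leaves 3.81 among the positives: e+ = 3.81/16.2 = 23.5%.
- Se′ = 0.95 × 0.765 / (0.95 × 0.765 + 0.05 × 0.95) = 0.7268/0.7743 = 93.9%
- Sp′ = 0.90 × 0.95 / (0.90 × 0.95 + 0.10 × 0.765) = 0.8550/0.9315 = 91.8%
- Histology-positive patients kept: 12 × 0.7743 = 9.3

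**Case 2: all six losses among LightPath-positives.** e+ = 6/16.2 = 37.0%, e− = 0.
- Se′ = 0.95 × 0.630 / (0.95 × 0.630 + 0.05) = 92.3%
- Sp′ = 0.90 / (0.90 + 0.10 × 0.630) = 93.5%
- Histology-positive patients kept: 12 × (0.95 × 0.630 + 0.05) = 7.8

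**Lower true sensitivity, 80%, at the Case 1 rates.** Se′ = 0.80 × 0.765 / (0.80 × 0.765 + 0.20 × 0.95) = 0.612/0.802 = 76.3%, about 76%.

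**Effect of x-ray-prompted shavings.** Suppose every LightPath-positive patient is shaved, a proportion L of shaved patients is imaged late, and a proportion q of LightPath-negative, histology-positive patients is shaved because of the x-ray. Then Se′ = Se(1−L) / [Se(1−L) + (1−Se)(1−qL)]. At L = 25%, Se′ is 93.4% for q = 0, 94.2% for q = 0.5 and 95.0% for q = 1. The bias in sensitivity shrinks as q rises and disappears only at q = 1.

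**The case against.** **The direction is not certain.** Surgeon discretion means that some LightPath-positive patients have no shaving, and x-ray findings put some LightPath-negative patients through the same hurdle. Both points stand, and both weaken the bias. To remove it, negatives would have to be shaved and imaged late as often as positives, which is not the workflow the Synopsis describes. The window is also only approximate, so the number of shavings that would count as late is unknown.

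**The shift is small against sampling error.** At 95% true sensitivity it is 1 to 3 points, while the exact 95% interval for 10 of 11 runs from 58.7% to 99.8%. No success threshold is attached to the primary measures, and PPV and NPV do not change when exclusion depends only on the LightPath result. This stands and limits the consequence. It does not justify a selection rule that serves no purpose for the WLE comparison.

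**The protocol already has safeguards.** Section 11.7.1 repeats the primary analysis on the ITT set and counts about 360 margins from 60 patients, section 8.6.4 records reasons for delay, and section 11.6.1 summarises the delayed set. The ITT repeat could expose the bias, but section 11.7 judges device performance on the primary analysis. The margin count does not say which set it uses, and the delayed-set summary covers only the decision to re-operate.

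**A stronger reading.** A reader might infer that the rule is bound to distort the results and could halve the histology-positive patients. With e+ = 50% and e− = 5%, sensitivity would be 90.9% and specificity 94.5%, with 6.3 histology-positive patients left. The documents do not support this as an expectation. That case loses 16.2 × 0.50 + 43.8 × 0.05 = 10.3 of 60 patients, or 17%, against the roughly 10% that section 11.8 anticipates.

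**Conclusion.** The rule is wrong as written: it conditions a WLE-only primary analysis on the timing of a later specimen whose existence depends mainly on the test result. The protocol fixes this rule itself, so it is not a detail left to the statistical analysis plan.

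Sensitivity is biased down and specificity up whenever LightPath-positive patients are excluded more often than LightPath-negative ones. The workflow makes that likely but does not guarantee it. Within the anticipated 10% loss and the planning assumptions, the two illustrative cases move sensitivity from 95% to about 94% or 92%, and specificity from 90% to about 92% or 93.5%. The fall in sensitivity is larger if true sensitivity is lower, and the shifts grow if losses exceed 10%. The exclusion rates are assumptions; only the conditional direction follows from the text.

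The follow-up-visit requirement, the two ITT definitions and the two forms of the imaging window are minor points. They do not support the bias mechanism, and their effect is not quantified.

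**What to change.** In section 11.6.1, with matching text in the Synopsis, define the primary-analysis set by the WLE specimen alone: a LightPath reading of the WLE, a histopathology result for it, and the timing criterion applied to the WLE image only. Apply the shaving-time criterion only to the cavity-shaving secondary outcome.

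In the same edit:
- Do not require the follow-up visit for the accuracy endpoints.
- Use one ITT definition in the Synopsis and section 11.6.1.
- Reconcile the target statements of the imaging time (4.1.2, 8.6.1, 8.6.2) with the limit statements (Synopsis, Study Procedures; 8.6.4), and use the reconciled rule for set membership.

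The cost is wording only. No new data are needed. The primary set gains any patient excluded solely for a late shaving or a missed follow-up visit.

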### 11.6.2. Sample Size Determination

The primary endpoint of the study is to report the sensitivity and specificity of CLI + FAR LightPath® imaging for tumour detection compared to positive tumour detection using standard-of-care histopathology methodology (positive margin of a WLE sample).

Using an estimate of the incidence of positive excision margins on histopathology as 20%, with 95%-confidence ( $\alpha = 0.05$  two-sided) and with 10% precision, a sample size of 54 patients will provide sufficient power to detect sensitivity of 95% and specificity of 90% (Cameron and Baldock 1998). To allow for any potential drop-out or non-analysable subjects a total sample size of 60 patients will be enrolled to attain  $N = 54$  patients in the analysis.

## 11.7. Data Analysis for Outcome Measures

Most data analysis will be descriptive only due to the non-comparative nature of this study. Continuous variables will be summarised descriptively by number of subjects, mean, standard deviation, minimum, and maximum. Categorical data will be summarised descriptively by frequencies along with associated percentages.

The primary outcome measure will be analysed on the per protocol analysis set. All other outcomes will be analysed based on the ITT set and on the per protocol analysis set (unless stated otherwise). The diagnostic performance of the LightPath® Imaging will be evaluated based on the primary endpoint analysis. Any other p-values presented from analysis of secondary endpoints will be used to aid interpretation and will not be adjusted for potential correlation between endpoints or multiple-testing.

Baseline participant characteristics will be summarized descriptively; continuous variables will be summarised descriptively by number of participants, mean, standard deviation, minimum, and maximum; categorical data will be summarised descriptively by frequencies along with associated percentages.

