### 11.7.2. Analysis of Secondary Outcome Measures

- Agreement between margin status of cavity shavings as determined by intraoperative CLI + FAR LightPath® imaging and post-operative histopathology will be assessed similarly to the primary outcome measure (section 11.7.1).
- Agreement between margin status of WLE specimens as determined by intraoperative CLI + FAR LightPath® imaging and routine intraoperative specimen x-ray will be assessed similarly to the primary outcome measure (section 11.7.1).

- Re-operation rate within the study cohort will be compared to the general breast cancer population undergoing a WLE at Guy's Hospital. The re-operation rate within Guy's Hospital is routinely recorded, audited and have remained consistent at 20 – 25% over many years.  
By recording the time required to intraoperatively image and assess each specimen, the average time added to the operating procedure can be determined.

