### 11.8. Termination / Drop-out

Recruitment will continue until up to 60 participants have been imaged. It is anticipated that approximately 10% of participants may drop out of the study or not be evaluable for the primary endpoint. The sample size of  $n = 54$  for the primary endpoint was selected including allowance of the assumption of 10% drop out. No other provision has been made for participant drop out. Patients who drop out will not be replaced.

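### The re-operation rate is set against a benchmark of women who had a WLE, but neither planned analysis set is defined as all women who had the study WLE, and the two ITT definitions conflict

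*Protocol*

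**What the plan says.** Re-operation is a secondary outcome. Section 11.7.2 says that the study rate "will be compared to the general breast cancer population undergoing a WLE" at the study hospital, where the audited rate is given as 20-25%.

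The analysis sets come from section 11.7, after the primary outcome has been placed on the per-protocol set: "All other outcomes will be analysed based on the ITT set and on the per protocol analysis set (unless stated otherwise"). The synopsis (2.3) also puts the secondary endpoints on both sets. Section 11.7.2 names no other set for re-operation.

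The sets are defined as follows:
- ITT, synopsis: "All patients who pass screening will be included in the intention to treat (ITT) population".
- ITT, section 11.6.1: "This will comprise all patients assigned to treatment".
- Per protocol, section 11.6.1: completion and compliance, and in addition "It includes only those participants whose WLE specimens, and cavity shavings (if any) specimens were imaged within the time-window of approximately 145 minutes post-injection".
- Delayed-image set, section 11.6.1: "A summary of the rate of decision to re-operate in the “Delayed LightPath® image set" is to be presented separately, "as these participants will be excluded from the per protocol analysis set".

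On losses, section 11.8 says: "It is anticipated that approximately 10% of participants may drop out of the study or not be evaluable for the primary endpoint".

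**The concern.** A rate compared with an external benchmark should count the same kind of person in its denominator. The benchmark is described as women undergoing a WLE. The two study sets differ from that in different ways.

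ITT is fixed before surgery. Screening is visit 1 and surgery is visit 2 (section 2.4), enrolment is the point of consent (section 8.8.1), and this single-arm protocol describes no separate step of assignment to treatment. A woman can therefore belong to ITT without having had the study WLE. If she never has a WLE she adds to the denominator and cannot add to the numerator.

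Per protocol selects on something that happens once surgery is under way. A woman leaves the set if her WLE specimen, or any cavity shaving, is imaged outside the window. Shavings are taken when LightPath or specimen x-ray indicates them (section 2.4), and they are imaged after the WLE specimen. The exclusion may therefore be related to margin status, and so to re-operation.

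Reduced re-operation is the first potential patient benefit listed in section 3.2.3, so readers will look closely at this comparison.

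**Working it through.** **The plan's own figure.** Sections 11.6.2 and 11.8 give 60 enrolled, 10% lost or not evaluable, and 54 analysed: 60 × (1 − 0.10) = 54. This reproduces. The plan gives no sample size, power or test for the re-operation comparison.

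**ITT.** Let p be the true rate among operated women and k the number of the 60 who never have a WLE. If those k count as not re-operated, the ITT rate is p × (60 − k)/60, which is too low by p × k/60. The protocol does not give k, so a range is shown.

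| k of 60 | ITT rate, p = 20% | ITT rate, p = 25% |
|---|---|---|
| 0 | 20.0% | 25.0% |
| 1 | 19.7% | 24.6% |
| 3 | 19.0% | 23.75% |
| 6 | 18.0% | 22.5% |

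The last row spends the whole 10% allowance on women who were never operated on. Section 11.8 also counts operated but non-evaluable women in that 10%, so k = 6 is an upper bound. The largest shift is 2.0 points at 20% and 2.5 points at 25%.

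A worked case with k = 6 and 12 re-operations: 12/54 = 22.2% (exact 95% CI 12.0-35.6%) among operated women, against 12/60 = 20.0% (10.8-32.3%) on ITT.

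**Per protocol.** Suppose all 60 are operated on, the overall rate is p, and d women are excluded for late imaging with RR times the re-operation risk of women imaged in time. The per-protocol rate is 60p / [(60 − d) + d × RR]. The protocol gives neither d nor RR; both are assumptions.

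| d | RR | Rate, p = 20% | Rate, p = 25% |
|---|---|---|---|
| 6 | 0.5 | 21.1% | 26.3% |
| 6 | 1 | 20.0% | 25.0% |
| 6 | 2 | 18.2% | 22.7% |
| 12 | 0.5 | 22.2% | 27.8% |
| 12 | 2 | 16.7% | 20.8% |

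The sign depends entirely on RR.

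**Effect on a conclusion, under an assumed test.** Take a one-sided exact binomial test at 5% and a device with no effect. With n = 60 the critical count is 6 at a 20% benchmark (actual size 3.1%) and 9 at 25% (4.5%). The chance of falsely declaring a reduction is P(X ≤ critical count) with 60 − k operated women.

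| k | Benchmark 20% | Benchmark 25% |
|---|---|---|
| 0 | 3.1% | 4.5% |
| 1 | 3.5% | 5.2% |
| 2 | 4.0% | 6.0% |
| 3 | 4.5% | 6.8% |
| 6 (upper bound) | 6.5% | 10.1% |

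**The case against.** A reader might infer that both planned comparisons favour LightPath, so that agreement between them would be false reassurance. The documents do not support this. They give no re-operation risk for late-imaged women. Late shavings may mark women with involved margins, but the shaving may itself have cleared the margin and spared a re-operation, and delay may be purely logistical. The per-protocol sign is open.

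A reader might also infer that the false-positive rate at least doubles. That needs all six women of the loss allowance to be never operated on, and a test that the plan does not specify; section 11.7 calls most of the analysis descriptive.

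Other points on this side carry weight. Under section 8.9, women who withdraw continue to receive standard care, so most would still have a WLE and could be re-operated; only cancelled or changed surgery dilutes the rate for certain. Section 11.8 speaks of recruiting until up to 60 have been imaged, which would imply that all 60 had a specimen excised, although section 11.6.2 says 60 enrolled. ITT as worded in 11.6.1 keeps late-imaged women and may come close to the operated set. The delayed-image summary is an honest disclosure. The audit's exact denominator is not shown beyond women undergoing a WLE. The SAP, which is not at hand, could use the allowance in 11.7 for exceptions.

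These points limit the size and remove the one-sided reading. They do not remove the mismatch. The protocol fixes the sets itself, defines ITT in two ways, and does not depart from those sets where it describes the re-operation comparison. The delayed-image summary does not restore the operated denominator: it reports decisions to re-operate, nothing says to combine it with the rest, and women outside per protocol for other reasons would still be missing.

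**Conclusion.** The point holds as a mismatch of denominators, not as a demonstrated bias towards the device. Neither set planned for the re-operation rate is defined as all women who had the study WLE, and the two ITT definitions conflict.

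For ITT, women who never have a WLE can only lower the rate. The shift is zero if all are operated on and at most 2.0 to 2.5 points at true rates of 20-25%. For per protocol the direction is unknown. Over the assumed range (6 to 12 women excluded, half to twice the risk) the rate runs from 16.7% to 22.2% for a true 20%, and from 20.8% to 27.8% for a true 25%.

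These shifts are small next to exact 95% intervals of about 21 to 24 points. The false-positive figures depend on the assumed test and, for ITT with one to three never-operated women, rise only modestly: from 3.1% to 3.5-4.5% at a 20% benchmark and from 4.5% to 5.2-6.8% at 25%. The case for changing the plan is that a better-matched denominator is available from data already collected.

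**What to change.** 1. Give ITT one definition, identical in the synopsis and section 11.6.1.
2. State in section 11.7.2 that the re-operation rate compared with the hospital benchmark is computed on all participants who underwent the study WLE, regardless of imaging time or any other per-protocol criterion.
3. Report the per-protocol and delayed-image rates as descriptive breakdowns of that total, without a benchmark comparison of their own.

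The cost is a harmonised definition and one sentence in 11.7.2, carried into the SAP. No new data are needed, because surgery and the MDT decision on re-operation are already recorded. The downside is that the reported rate may be slightly less favourable than the one from the sets now planned.
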